## 2 OBJECTIVES AND ENDPOINTS

### 2.1 Primary Objectives

- To compare the EndoBarrier with conventional medical therapy, diet and exercise for obesity related type II diabetes and their effectiveness on metabolic state as defined by the International Diabetes Federation (IDF) with an HbA1c reduced by 20%.

### 2.2 Secondary objectives

- To compare the EndoBarrier with conventional medical therapy, diet and exercise for obesity related type II diabetes and their effectiveness on:
  - Metabolic state as defined by the International Diabetes Federation (IDF) with an HbA1c < 6% ( or < 42 mmol/mol)
  - Blood pressure < 135/85
  - Absolute weight loss
- To investigate the mechanism of the effect of the EndoBarrier via changes in:
  - Gut hormones
  - Microbiome
  - Appetite, food hedonics and brain reward systems
  - Body fat content
  - Food preference
  - Hepatic or peripheral insulin sensitivity
  - Bile acids
  - Biomarkers such as genetic markers
- To estimate the cost-effectiveness of the EndoBarrier device compared with conventional treatment over the trial period (within trial analysis).
- To estimate the long-term cost-effectiveness (over 24 months) of the EndoBarrier device compared with conventional treatment and alternative surgical interventions.

### 2.3 Safety objective

- To evaluate the safety of the EndoBarrier and frequency of adverse events

### 2.4 Primary Endpoints

- Reduction in HbA1c by 20%

|                                                                                   |                                                                             |                                    |                                               |                                            |
|-----------------------------------------------------------------------------------|-----------------------------------------------------------------------------|------------------------------------|-----------------------------------------------|--------------------------------------------|
| [figure not shown] | Title:
EndoBarrier TM
Gastrointestinal Liner
Diabetes Trial | Protocol No:
Version 5.0 | Sponsor:
Imperial College
London | Date:
5 th March 2018 |
|-----------------------------------------------------------------------------------|-----------------------------------------------------------------------------|------------------------------------|-----------------------------------------------|--------------------------------------------|

## 2.5 Secondary Endpoints

- HbA1c of less than 6% (or 42 mmol/mol)
- Blood pressure below 135/85 mmHg
- Absolute weight loss greater than 15%
- Reduction in dose/or number of medications
- Frequency of Adverse Events
- Cost of interventions and related health and social care
- QALYs accrued (calculated from area under the EQ-5D curve)
- Incremental cost per QALY within the trial period and over the long-term

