and all four patients with T2DM had normal fasting glucose levels without hypoglycaemic medication. In subsequent trials obese patients lost 11.9% excess weight compared to 2.7% for the sham arm treated with diet alone. In a similar Dutch study the mean excess weight lost was 19% v 6.9% for controls. For the eight subjects with T2DM in that study six had improvements in their T2DM (reduced HbA1c levels) and one managed to achieve diabetes resolution.

In addition to the Imperial pilot study, the only similar study to that proposed to date is a small Dutch study. The device was implanted for a six month period with 34 patients in the treatment and control arms. At six months there was a fall of 1.3% in the HbA1c in the EndoBarrier arm and 0.8% in the control arm, showing the benefit of regular supervision and dietetic advice. This study has only been presented in abstract form (Koehestanie, P Diabetes 2012 Suppl P1183 A305). In this study only one patient required removal of the device before the end of the six month study period.

A further Chilean study implanted the device in 39 morbidly obese subjects (6 with T2DM) for 52 weeks. For those that completed the study, the average weight loss was 22kg. To date only 19 subjects with T2DM have had the device in situ for a year.

Pilot data and clinical observations from a cohort of patients at Imperial College London suggest that bypassing the proximal small bowel with the EndoBarrier results in:

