Conservatively, it was estimated that 15% of patients in the control arm will achieve the target but believe this to be an overestimate. The Steno study  is the best quality randomised study (80 patients in each arm) into the effect of best medical therapy published to date and demonstrated over an average 7.8 years significant improvements in HbA1c amongst those having intensive medical therapy from 8.4+/- 1.6 to 7.7+/-1.2, but no change in HbA1c amongst those continuing with standard medical therapy. This study defines the very best that could realistically be achieved in the control arm, but expect there to be very little if any change in this group. The reporting of HbA1c as an outcome measure was not in accordance with the newly defined IDF criteria, but considering the small average reduction achieved in the Steno study, it will be assumed that a target of 15% of patients reaching the endpoint is a conservative estimate. Company data on the small number of patients who have reached a year with the device in place suggest that 40% will achieve this target.

According to our own experience with the device in the commercially sponsored study, up to 30% of patients in the treatment group may have the device removed early. Nevertheless other commercially sponsored (unpublished) studies of this device have achieved lower explant rates ([name] – GI Dynamics). We have therefore diluted the treatment effect from 40% vs. 15% to 35% vs. 15% achieving the target of 20% reduction in HbA1c for treatment arm vs. standard arm. 73 patients per group will give 80% power to detect a significant effect. Adding 10% loss of follow-up increases the sample size to 80 per group.

The dilution was calculated starting from the assumption that 40% of patients with the device will reach the target (this estimate is based on company data based on diabetic patients in the same range of BMI as in the present proposal). If 30% of patients in the treatment group need to remove the device early but remain available for follow-up, in the worst case scenario, the proportion reaching the target is the same as in the control group, bringing the estimate for the treatment group to 32.5%. However most of them will keep the device for some time, having some benefit, so it is plausible to assume that the estimate is higher than 32.5%.

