## 8.2 Data Analysis

Patient characteristics will be summarized. Summaries of continuous variables will be presented as means and standard deviations if normally distributed, and as medians and inter-quartile ranges for skewed data, whilst categorical variables will be presented as frequencies and percentages. The difference between the two study groups in the proportion of patients achieving substantial improvement in the metabolic syndrome both at 12 and 18 months will be analysed using logistic regression adjusting for the stratification variables (BMI groups and sites). Analysis of secondary outcomes will be conducted using standard statistical procedures applicable to categorical or continuous data as appropriate. For missing values we will explore the pattern and the extent of missingness and we will carry out an appropriate form of multiple imputation if required. The analysis will be performed according to the intention to treat principle. All statistical tests will be two-tailed with a 5% significance level.

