#### Appetite food hedonics and brain reward systems:

Comparison of brain activation during fMRI paradigms and outcomes from behavioural measures of food hedonics and questionnaires will be compared between groups using a 2x2 ANOVA design including group (control vs. Endobarrier) between subject factor, time (baseline vs. follow-up visit) within subject factor, and group x time interaction to identify differential effects between groups. For fMRI studies analysis will use region of interest analyses (e.g. for food pictures orbitofrontal cortex (OFC), amygdala, caudate, nucleus accumbens and anterior insula; for MID task nucleus accumbens, dorsal striatum and OFC; for Go-NoGo task pre-supplementary motor area). In addition whole brain analysis will be performed to compare groups using statistical thresholds of voxel-wise correction FDR  $P < 0.05$  and cluster-wise correction  $Z > 2.3$   $P < 0.05$ . In addition linear regression will be performed to measure the correlation of variables at baseline or during the intervention with primary outcomes at 1 year e.g. weight loss and decreases in HbA1c within each group, to generate predictive markers and generate mechanistic hypotheses.

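### The weight endpoint is a yes/no 15% cut with no stated base, baseline visit or time point, while the objective has no cut-off; dichotomising costs power, by an amount the protocol's figures do not settle

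*Protocol*

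**What the plan says.** The weight outcome appears in three places in the protocol.

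- **Section 2.2, secondary objectives:** "Absolute weight loss". It has no threshold, unit or time point. The HbA1c and blood pressure items beside it do carry thresholds.
- **Section 2.5, secondary endpoints:** "Absolute weight loss greater than 15" per cent. This is a responder definition. It names neither the weight of which 15% is taken, nor the baseline visit, nor the assessment visit.
- **Section 8.2, the paragraph on appetite, food hedonics and brain reward:** variables are to be correlated "with primary outcomes at 1 year e.g. weight loss and decreases in HbA1c within each group". The only declared primary endpoint is in section 2.4, "Reduction in HbA1c by 20" per cent, and section 8.1 sizes the trial on that alone.

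Weight is scheduled at V1 to V4 and at every later clinic visit (Table 2). The device is removed at 12 months, and follow-up continues to 24 months (section 3.1).

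**The concern.** An objective without a cut-off and an endpoint with one can be read as two outcomes, an amount and a success rate. The endpoint itself is not computable as written, for three reasons.

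- **Base.** The word absolute sits oddly with a percentage. Section 1.2 reports both of its controlled weight results as excess weight, so the base needs to be written down.
- **Baseline.** Four weights precede or coincide with the start of treatment, and V4 falls after 7 days of liquid diet.
- **Time.** A result at 12 months, with the device in place, answers a different question from one at 24 months.

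If these stay open, the measure reported could be settled after the data are seen. Reducing weight is a central hypothesis of the trial (section 1.4). If the responder version is the only one analysed, a real difference in mean weight may go undetected because few patients in either arm pass the cut.

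**Working it through.** **The plan's own figure.** Section 8.1 assumes "35% vs. 15% achieving the target of 20% reduction in HbA1c" per cent, and section 8.2 states "All statistical tests will be two-tailed with a 5% significance level". The pooled two-proportion formula gives n = [1.960·√(2·0.25·0.75) + 0.842·√(0.35·0.65 + 0.15·0.85)]² / 0.20² = 72.4, so 73 per group, as stated. With 80 per group and 10% lost, 80 × 0.9 = 72 are evaluable. This concerns HbA1c only; the protocol gives no power for weight.

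**How much the base matters.** Take excess weight as weight above BMI 25 (assumption). Then total loss = excess loss × (BMI − 25)/BMI. At BMI 40 the factor is 15/40 = 0.375, so 15% of total weight is 15/0.375 = 40% of excess weight. Over the eligible range it runs from 90% (BMI 30) to 30% (BMI 50). The average device patient in the Dutch study ("In a similar Dutch study the mean excess weight lost was 19% v 6.9% for controls") passes a 15% cut on excess weight. At BMI 40 the same patient has lost 19 × 0.375 = 7.1% of total weight and fails.

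**Power from the two controlled results.**

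- From section 1.2: excess loss of 19% v 6.9% (Dutch study) and 11.9% v 2.7% (sham-controlled study).
- Assumed, because the protocol gives none of them: mean BMI 35 to 43, normally distributed loss, SD 5 to 8 points of total weight.
- Responder rate = 1 − Φ((15 − mean)/SD), compared by the two-proportion normal approximation.
- Power for the mean difference = Φ(difference/(SD·√(2/72)) − 1.96).

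Worked case, Dutch result, BMI 40, SD 6:

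- Means are 7.125% and 2.59%; responder rates are 9.5% and 1.9%.
- Responder: standard errors 0.0386 (null) and 0.0381 (alternative), so power = Φ((0.0754 − 1.96·0.0386)/0.0381) ≈ 50%. Fisher's exact test gives 34%.
- Mean difference: 4.54/(6·√(2/72)) = 4.54, so power = Φ(4.54 − 1.96) ≈ 99%.

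| Prior result | Responder >15% | Mean difference |
|---|---|---|
| Sham-controlled, 11.9% v 2.7% | 9–31% | 50–100% |
| Dutch, 19% v 6.9% | 19–64% | 74–100% |

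Over this grid the mean difference always has more power.

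**The 52-week result.** Section 1.2 also reports an average loss of 22 kg in completers, without baseline weight, SD or control arm. Assume a baseline of 110 to 160 kg, control loss of 0 to 5% and SD of 5 to 10, and count the 30% early removals of section 8.1 as controls. Mean loss while the device is kept is then 22/160 = 13.75% to 22/110 = 20%.

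- Least favourable case (160 kg, control loss 5%, SD 10): responder rates are 0.7 × 45.0 + 0.3 × 15.9 = 36.3% against 15.9%, with power of 80%.
- Over all combinations, responder power is 80 to 100%.
- Mean difference in the least favourable case: 0.7 × (13.75 − 5) = 6.125, and 6.125/(10·√(2/72)) = 3.675, so power = Φ(3.675 − 1.96) ≈ 96%.

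**Choice of baseline.** V3 looks like the natural weight before the diet, but it follows randomisation, disclosure of the arm at V2 (section 5.2) and dietary counselling at V2 (section 5.5.3). Its window also reaches the diet. V3 may fall as late as day −14 + 7 = −7. V4 may fall as early as day −3, which starts the diet at day −10. V1 is free of both problems.

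**The case against.** - **Section 2.2 may name the domain and 2.5 the measure.** This is fair. Section 2.2 never says that the outcome is continuous; that is an inference from the missing cut-off. The base, baseline and time point are still absent from 2.5.
- **Absolute may mean total as opposed to excess weight.** Given the vocabulary of section 1.2 this is the likelier reading, and the calculation uses it. It should be stated.
- **The power contrast rests on numbers the protocol does not contain.** This stands. A reader of the two controlled results might infer that the 15% endpoint is bound to miss a real effect which a mean comparison would almost surely show. The documents do not support that: they give no SD and no mean BMI, power for the mean difference can be as low as 50%, and the 22 kg result gives the responder good power. That result is uncontrolled and from completers, so it does not prove high power either.
- **Section 8.2 could be read as making weight a second primary.** It does not. The phrase sits in a hypothesis-generating, within-group regression, and sections 2.1, 2.4 and 8.1 consistently give HbA1c as the primary.
- **Covariates and baseline visit often belong in the SAP, which is not shown.** This is true of the model. However, section 2.5 itself fixes the endpoint as a responder, and an SAP would have to depart from it to analyse weight as measured.

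**Conclusion.** The point holds as one of definition and efficiency for a secondary endpoint. The objective has no cut-off, the endpoint has one, and the endpoint lacks a base, a baseline visit and a time point. Dichotomising loses power: on the controlled prior results about 9 to 64% for the responder against 50 to 100% for the mean difference, with 72 per arm, mean BMI 35 to 43 and SD 5 to 8 points, all but the first being assumptions. Because the 52-week result gives the responder about 80 to 100%, low power is a risk and not a demonstrated fact. The mean comparison is no worse in any case examined. The primary analysis and the sample size are untouched, and the wording in section 8.2 is a minor slip.

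**What to change.** In sections 2.2 and 2.5, define the weight endpoint as percent change in total body weight from the pre-randomisation screening weight (V1) to 12 months. Compare the arms by a linear model adjusted for baseline weight, BMI stratum and site. Keep loss of more than 15% of total body weight, from the same baseline and at the same time point, as a supportive responder summary, and drop the word absolute. In the brain reward paragraph of section 8.2, refer to clinical rather than primary outcomes at 1 year.

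No new data are needed, since weight is already scheduled at these visits. The cost is a wording amendment and one additional reported analysis.

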## 3 STUDY DESCRIPTION

### 3.1 Design

This study is a randomised controlled trial of the EndoBarrier device compared with standard medical therapy for the management of obese subjects with T2DM. Subjects will be randomised to one of the two treatment arms (see Table 1) of the study via the InForm system (the eCRF database for the study). Over 24 months, the study will be performed at two investigational sites, Imperial College Healthcare NHS Trust in London and University Hospital Southampton NHS Foundation Trust.

Individuals in both study arms will be invited regular medical check-ups including measurement of weight, blood pressure, and blood parameters (HbA1c, cholesterol, triglycerides, fasting blood glucose, insulin), quality of life (EQ-5D) and use of health services, as well as to record any adverse events and medications. Diabetes medication titrations will be conducted by the study diabetologists/endocrinologists in accordance with the guidelines of the American Diabetes Association (see section 5.5.1 for full details). They will also receive routine dietary and exercise counselling as well as telephone counselling from a specialist dietitian. The control arm will be invited for routine follow-up visits to review their standard medical care. Both arms will also be invited to undergo a diversity of tests investigating the mechanism of the EndoBarrier. After 12 months, the EndoBarrier will be removed and both arms will be followed up for a remaining 12 months.

In order to investigate the mechanism of the effect of the EndoBarrier Device, the trial is divided into three sub-groups in each arm who will have the following additional assessments at visits 3, 5, 8 and 10, 14 (see section 5.4 and 5.6 for more detail):

- Sub-group 1 (minimum n=24): functional MRI, eating behaviour, cognitive assessment, and post-meal gut hormones
- Sub-group 2 (minimum n=18): insulin clamps

|                                                                                   |                                                                             |                                    |                                               |                                            |
|-----------------------------------------------------------------------------------|-----------------------------------------------------------------------------|------------------------------------|-----------------------------------------------|--------------------------------------------|
| [figure not shown] | Title:
EndoBarrier TM
Gastrointestinal Liner
Diabetes Trial | Protocol No:
Version 5.0 | Sponsor:
Imperial College
London | Date:
5 th March 2018 |
|-----------------------------------------------------------------------------------|-----------------------------------------------------------------------------|------------------------------------|-----------------------------------------------|--------------------------------------------|

- Sub-group 3 (minimum n=18): assessment of taste and food preference, eating behaviour assessment, and post-meal gut hormones

Participation in the sub-groups is optional.

### 3.2 Treatment regimens

**Table 1. Summary of treatment groups**

| Treatment Sequence         | Number of subjects * | Treatment Period
1 | Follow-up Period
2 |
|----------------------------|----------------------|-----------------------|-----------------------|
| 1 EndoBarrier Device       | 80                   | 12 months             | 12 months             |
| 2 Standard Medical therapy | 80                   | 12 months             | 12 months             |
| Total number of subjects   | 160                  |                       |                       |

\* Additional subjects may be randomised to allow for any randomised subject that has withdrawn prior to commencement of treatment at Visit 4.

|                                                                                   |                                                                                                |                                           |                                                             |                                                  |
|-----------------------------------------------------------------------------------|------------------------------------------------------------------------------------------------|-------------------------------------------|-------------------------------------------------------------|--------------------------------------------------|
| [figure not shown] | Title:
EndoBarrier™
Gastrointestinal Liner
Diabetes Trial | Protocol No:
Version 5.0 | Sponsor:
Imperial College
London | Date:
5th March 2018 |
|-----------------------------------------------------------------------------------|------------------------------------------------------------------------------------------------|-------------------------------------------|-------------------------------------------------------------|--------------------------------------------------|

### 3.3 Study flow chart

[figure not shown]

|                                    |                                                                             |                                    |                                               |                                            |
|------------------------------------|-----------------------------------------------------------------------------|------------------------------------|-----------------------------------------------|--------------------------------------------|
| Imperial College
London | Title:
EndoBarrier TM
Gastrointestinal Liner
Diabetes Trial | Protocol No:
Version 5.0 | Sponsor:
Imperial College
London | Date:
5 th March 2018 |
|------------------------------------|-----------------------------------------------------------------------------|------------------------------------|-----------------------------------------------|--------------------------------------------|

[figure not shown]

**Legend:**

A = Weight, waist, blood pressure, routine bloods, adverse events, changes in medication/medical history  
B = Dietary Counselling  
C = Medical Therapy (Diabetologist/Endocrinologist)  
D = Gastroenterologist  
E = Dietitian follow up  
F= Bioelectrical impedance  
G= fMRI  
H = Gut hormones(fasting and post-meal profile)  
I= Gut hormones(fasting only)  
J = Metabolomics  
K = Health Economics questionnaires  
L = Eating and behaviour questionnaires  
M = Insulin clamps  
N= Eating behaviour computerised tasks  
O= Cognitive assessment tasks  
P= DNA Sample  
Q= Food preference and taste assessment  
R= Telephone counselling

|                                                                                   |                                                                             |                                    |                                               |                                            |
|-----------------------------------------------------------------------------------|-----------------------------------------------------------------------------|------------------------------------|-----------------------------------------------|--------------------------------------------|
| [figure not shown] | Title:
EndoBarrier TM
Gastrointestinal Liner
Diabetes Trial | Protocol No:
Version 5.0 | Sponsor:
Imperial College
London | Date:
5 th March 2018 |
|-----------------------------------------------------------------------------------|-----------------------------------------------------------------------------|------------------------------------|-----------------------------------------------|--------------------------------------------|

